## **Section 11. Adverse Events**

### **11.1 Definition and Classification**

Adverse event (AE) refers to any unfavorable and unintended sign (including an abnormal laboratory finding), symptom, or disease temporally associated with the use of a medical treatment or procedure in a patient or clinical investigation subject, whether or not related to the medical treatment or procedure. AEs are usually graded by the severity:

- ① Mild AEs: asymptomatic or mild symptoms; observations only; intervention not indicated.
- ② Moderate AEs: minimal or local intervention indicated; limiting instrumental activities.
- ③ Serious AEs (SAEs): AEs that (1) results in death, (2) is life-threatening, (3) requires inpatient hospitalization or causes prolongation of existing hospitalization, (4) results in persistent or significant disability, (5) may have caused a congenital anomaly or birth defect, or (6) requires intervention to prevent permanent impairment or damage.

In this study, the AEs are classified into intervention-related AEs (only occurrence in intervention group and probably related to the intervention) and common AEs (occurrence in both groups, whether or not increased with intervention). Possible intervention-related AEs include fainting, allergic reaction, pain at injection site, knee swelling, decreased range of motion, and infection at injection site. Because of the study population (patients with ACL injuries and undergoing ACLR), common AEs should include all complications and unfavorable outcomes accompanied with ACL injuries as well as those with ACLR, such as graft failure, residual laxity, decreased range of motion, and arthrofibrosis.

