#### ③ P4 score for pain, at 3, 6, and 12 months

The visual analog scale (VAS) for pain is assessed on a straight horizontal line; scores range from 0 (no pain) to 10 (worst pain possible), with 1–3 indicating mild pain, 4–6 indicating moderate pain, and 7–10 indicating severe pain. To comprehensively evaluate the pain in different timing and conditions, the P4 score is calculated as the sum of VAS scores at 4 timepoints (morning, afternoon, evening, and with activity) during the past 2 days.

④ Tegner score, at 3, 6, and 12 months

Tegner Activity Scale assesses the highest level of current sports participation. Scores range from 0 (sick leave or disability) to 10 (professional level of competitive sports), with higher values indicating higher levels of sports activities, and scores  $\geq 6$  are considered as return to pivoting sports. The MCID (as minimally detectable) for Tegner score is 1.

⑤ Lysholm score, at 3, 6, and 12 months

Lysholm Knee Questionnaire is specifically designed for ligament injuries and includes 8 items regarding subjective perceptions (such as instability, pain, and locking). Scores range from 0 to 100, with higher values indicating fewer symptoms and better knee function in daily living. The MCID for Lysholm score is 10.7 (distribution-based, from our data).

⑥ Subjective IKDC score, at 3, 6, and 12 months

IKDC Subjective Knee Form includes 18 items covering 3 domains (symptoms, sports activities, and function). Scores range from 0 to 100, with higher values indicating better knee conditions. The MCID for IKDC score is 10.4 (distribution-based, from our data).

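### The severity scale for adverse events ends in the definition of seriousness, so a severe but non-serious reaction has no grade

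*Protocol*

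**What the plan says.** Section 11.1 introduces its list with the statement that "AEs are usually graded by the severity". Three levels follow:

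- Level 1: "Mild AEs: asymptomatic or mild symptoms; observations only; intervention not indicated".
- Level 2: "Moderate AEs: minimal or local intervention indicated; limiting instrumental activities".
- Level 3 opens with "Serious AEs (SAEs): AEs that (1) results in death, (2) is life-threatening" and goes on through four further criteria. They include "requires inpatient hospitalization or causes prolongation of existing hospitalization" and, as the last, "requires intervention to prevent permanent impairment or damage".

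The same section then sorts events by their relation to the intervention and names the reactions it expects: "Possible intervention-related AEs include fainting, allergic reaction, pain at injection site, knee swelling, decreased range of motion, and infection at injection site".

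Section 11.2 lists what goes on the case report form for each event: timing, manifestation, treatment and its duration, relation to the intervention, and outcome. Neither a severity grade nor a seriousness flag is in that list. Section 11.2 also requires an SAE form and a report to the institutional review board within 24 hours for serious events. Section 12.1, under other variables, plans a chi-square or Fisher exact comparison of adverse events and does not mention severity.

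**The concern.** Severity is how intense an event is. Seriousness is whether the event had, or threatened, one of a fixed set of outcomes. An event can be severe without being serious, and serious without being severe. The list in 11.1 uses the first idea for its two lower levels and the second for its top level, so the steps do not form one scale.

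This matters more here than in many trials because only one arm is injected, three times (sections 8.1 and 8.2). Local reactions to the injection are therefore the harms most likely to differ between the arms, and they are the kind of event that can be intense without leading to admission or lasting damage. If such events have no grade, the trial has no defined way to say how intense the injection reactions were in each arm.

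**Working it through.** There is no figure to reproduce. The check takes the three definitions in 11.1, asks which axis each uses, and runs two test cases through them.

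**Axis of each level**

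| Level | Defined by | Axis |
|---|---|---|
| Mild | symptoms, no treatment needed | severity |
| Moderate | small or local treatment, limits on instrumental activities | severity |
| Serious | six outcome criteria | seriousness |

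The axis changes at the last step, and no level is called severe.

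**Case 1: intense, not serious.** Take a reaction after an injection that limits self-care and needs more than small or local treatment. It involves no admission, threat to life, lasting disability, birth defect or risk of permanent damage.

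- Mild: no, because treatment is needed.
- Moderate: no, because it exceeds both parts of "Moderate AEs: minimal or local intervention indicated; limiting instrumental activities".
- Serious: no, because none of the six criteria is met. The last one covers treatment only where it "requires intervention to prevent permanent impairment or damage".

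The event has no level. In practice it is left ungraded or recorded as moderate.

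**Case 2: mild, but admitted.** Take a faint, which is on the list of expected reactions, followed by a short inpatient stay for observation.

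- By intensity it fits the mild wording.
- It also meets "requires inpatient hospitalization or causes prolongation of existing hospitalization", a criterion with no condition on intensity.

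The event takes the top level of a scale introduced as one of severity, although its intensity is mild.

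**Search for a repair elsewhere.** The relation-based classification in 11.1 answers a different question. The form items in 11.2 contain no severity grade. Section 12.1 adds none. The list in 11.1 is the only severity scale for adverse events in the protocol.

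**The case against.** The strongest reply is that the list has little work to do. Its lead-in says how events are usually graded, the classification labelled as this study's own is by relation to the intervention, the form items omit severity, and no table by severity is planned. This largely stands. It limits the consequence to the quality of harm description, and it means that no promised output is broken. It does not remove the fault, because the only severity scale in the document is still wrongly built and its third level carries the operative SAE definition.

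Four other limits also stand:

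- The gap is narrower than all severe, non-serious events. An intense local reaction that is managed locally can fit the moderate wording. Only reactions beyond that wording fall out.
- Information is not necessarily lost. Section 11.2 asks for manifestation, treatment, duration and outcome in detail, so intensity could be reconstructed later. Range of motion and knee circumference are measured at each follow-up (10.4). This backstop is partial: injections are given after the assessments at a visit (8.1), so a short flare could pass between visits.
- A reader might infer that severe reactions will be pushed up into the SAE category and inflate SAE counts. The text does not support that, since an event meeting none of the six criteria is not an SAE. Likewise, the admitted faint is correctly an SAE and would remain one after the fix.
- A reader might see a contradiction with section 10.2, where a pain score has a band of "7–10 indicating severe pain". That is a band of an outcome measure. It does not bear on how adverse events are graded.

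**Conclusion.** The point holds as a fault in the definition of adverse-event severity. Section 11.1 names severity as its basis but defines the top level by seriousness. As a result, one kind of event has no grade and another takes a level that does not reflect its intensity. Both follow from the wording alone.

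The size is modest. What suffers is the description, by arm, of how intense the injection reactions are. The SAE criteria, SAE counts, expedited reporting, primary analysis and sample size are unaffected. How many events would be misplaced cannot be derived from the protocol, which gives no expected rate of reactions by intensity; it could be none. The conclusion assumes only that some expected reaction can exceed the moderate wording without meeting a seriousness criterion, which is plausible for the allergic, pain, swelling and infection events that the protocol itself lists.

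The change is worth making because it is cheap and only one arm is exposed to the injections. It is a correction to safety wording and does not cast doubt on the trial's main conclusion.

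**What to change.** In section 11.1, replace the single list by two separate items for every event:

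- **Severity:** mild, moderate or severe. Keep the mild and moderate definitions. Define severe on the same axis of treatment needed and activity limited, as exceeding the moderate wording, whether or not the event is serious.
- **Seriousness:** yes or no on the six existing criteria, unchanged.

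Add both items to the case report form list in section 11.2. Keep the SAE form and the 24-hour report tied to seriousness only. Tabulate both items by arm.

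The cost is the wording in 11.1 and 11.2, two added form fields and one more descriptive table. No extra visits or measurements are needed.

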## Section 1. Introduction

Anterior cruciate ligament (ACL) injury is one of the most common sports injuries of the knee joint. There is an increasing incidence of ACL injuries, with approximately 60,000 to 200,000 per year in the United States, especially for teenagers. With the incidences of sports injuries increasing gradually in China, the public have paid more attention to the functional recovery of sports activities, and ACL reconstruction (ACLR) has become a conventional surgery performed in sports medicine. In ACLR, autologous tendons are usually harvested and prepared into several-stranded grafts, which are passed through the tibial and femoral tunnels and fixed by suspension or extrusion. Afterwards, the grafts undergo a series of biological tendon-to-bone healing processes (termed “ligamentization”, a transformation from tendons to the functional ACL), including avascular necrosis in the early healing stage, proliferation and revascularization in the remodeling stage, and restoration of histological and biomechanical properties in the maturation stage. Factors associated with unfavorable graft remodeling and maturation (biological recovery) after ACLR include graft impingement, sports reinjury, and residual knee laxity. Furthermore, edema and adhesions are common postoperative reactions, causing symptoms of knee swelling, pain, and limited range of motion as well as hampering the functional recovery. To prevent the development of adverse outcomes (such as graft failure, arthrofibrosis, and osteoarthritis), timely intervention should be taken, including medications, physical therapy, and arthroscopic surgeries.

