## **11.2 Record and Report**

Once an AE occurs, the time of occurrence, clinical manifestation, treatment process and duration, relation with intervention, and outcome of the AE should be recorded in detail on the case report form. After an unintended sign (such as laboratory test abnormalities) occurs, the patient must be followed up until the test results return to normal, or return to pre-intervention levels, or the AE is determined to be unrelated to the intervention. In cases of SAEs, an SAE form must be filled in and reported to the institutional review board (IRB) (within 24 hours) and National Medical Products Administration (if applicable).

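### Section 11.1 makes absence from the control arm a condition for calling an adverse event intervention-related, so an excess of swelling or stiffness under PRP would be labelled common

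*Protocol*

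**What the plan says.** Section 11.1 defines two classes. The first is "intervention-related AEs (only occurrence in intervention group and probably related to the intervention"; both conditions must hold. The second is "common AEs (occurrence in both groups, whether or not increased with intervention".

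The section then gives examples. For the first class: "Possible intervention-related AEs include fainting, allergic reaction, pain at injection site, knee swelling, decreased range of motion, and infection at injection site". For the second, complications of the injury and of the reconstruction, "such as graft failure, residual laxity, decreased range of motion, and arthrofibrosis".

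Three other places bear on this:

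- Section 1 states that "edema and adhesions are common postoperative reactions, causing symptoms of knee swelling, pain, and limited range of motion".
- Section 11.2 requires for each event that its "relation with intervention, and outcome of the AE should be recorded in detail on the case report form".
- Section 12.1 (Other variables) plans a chi-square or Fisher exact test for categorical variables and names adverse events among them.

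Section 11.1 also grades events by severity in three steps: mild, moderate and serious. The third step is defined by six seriousness criteria, such as death, hospitalisation or lasting disability.

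**The concern.** Whether a treatment causes an event and whether untreated patients also have it are separate questions. For an event with a background rate, harm shows as a higher rate in the treated arm. Section 11.1 sets that evidence aside: presence in both groups decides the class, and an increase is expressly declared irrelevant to it.

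The events affected are those where harm from an intra-articular injection and the ordinary course after surgery look alike, namely swelling and loss of motion. If PRP made either more frequent, a safety summary built on these classes would show the excess under a heading that suggests background.

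A smaller defect sits in the same section. Because the grading goes from moderate to serious, a severe event that meets none of the six criteria has no grade, and a serious event carries no severity grade.

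**Working it through.** **1. The rule against the protocol's own lists.**

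| Event | Listed as possibly intervention-related | Listed as common | Expected after surgery (Section 1) |
|---|---|---|---|
| Decreased range of motion | yes | yes | yes |
| Knee swelling | yes | no | yes |
| Fainting, allergic reaction, injection-site pain, injection-site infection | yes | no | not mentioned |

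Decreased range of motion stands in both classes, although the definitions exclude each other. Knee swelling stands in a class that it can keep only if no control has it, while Section 1 leads one to expect it in controls. So two of the six listed events are in conflict with the definition. The two injection-site events are not affected, since controls receive no injection.

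**2. The rule against Section 11.2.** Relation to the intervention is recorded for each event. On the literal reading, the Section 11.1 class depends on what happens in the other arm and may not be known until follow-up there is complete. An event judged related on the form could then end up as common.

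**3. How often the rule would block the label.** The protocol gives no figure for this. The only input from it is the arm size in Section 5: 51 per group, and 51 / 0.85 = 60 with 15% dropout, which reproduces. The control rate p is an assumption, because the protocol states none.

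P(at least one control case) = 1 − (1 − p)^n

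- p = 5%, n = 60: 1 − 0.95^60 = 0.954
- p = 10%, n = 60: 1 − 0.90^60 = 0.998

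| Assumed control rate | n = 60 | n = 51 |
|---|---|---|
| 1% | 45% | 40% |
| 2% | 70% | 64% |
| 3% | 84% | 79% |
| 5% | 95% | 93% |
| 10% | 99.8% | 99.5% |

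**4. What the planned test would show beside the label** (illustrative counts, PRP against control; all are common under the rule):

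- 15/60 against 3/60: chi-square p = 0.002, Fisher p = 0.004
- 10/60 against 1/60: Fisher p = 0.008
- 6/60 against 1/60: Fisher p = 0.11

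Approximate power of a two-sided 5% comparison with 60 per arm (normal approximation, assumed rates) is 18% for 5% against 10%, 45% for 5% against 15%, and 70% for 5% against 20%. A large excess would be flagged despite the label. A moderate one often would not be, and then the label carries more weight.

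**The case against.** The strongest reply is that nothing is lost. Relatedness is recorded per event (Section 11.2). Adverse events are tested between arms, and nothing restricts that test to one class (Section 12.1). Knee circumference and range of motion are secondary outcomes at every follow-up in both arms (Section 10.4), measured by examiners who are to be blinded (Section 7.2). This stands. A reader might infer from Section 11.1 that an increase under PRP could not be detected or reported; the documents do not support that. One limit remains: at 4 weeks, 8 weeks and 3 months the injection follows the assessment (Section 8.1), so a brief reaction after injection may be missed by the examinations.

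A reader might also infer that a single chance event in the PRP arm would automatically count as intervention-related. It would not, because the definition also requires a probable relation.

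Finally, Section 11.1 does not say whether the class applies to one event or to an event type, or when it is assigned. It may have been meant as two reporting headings, one for reactions to the procedure and one for complications of surgery. Decreased range of motion could then appear under both. This reading is possible, but the text does not state it, and it does not account for the clause that sets an increase aside. The probabilities above rest on the literal reading by event type.

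**Conclusion.** The point holds as a defect of classification. As written, Section 11.1 would almost never allow swelling or reduced motion to be classed as intervention-related, even if PRP increased them: the label is blocked with probability 95% at an assumed 5% control rate and 99.8% at 10%. For rarer events the block is less certain (45% at 1%). The figures assume the literal reading and independent events among 60 controls. The conflict between the definitions, the two lists and Section 11.2 needs no assumed rate.

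The consequence is a misleading label in the safety summary. It would be going too far to treat this as a threat to the trial's main conclusion: the primary outcome analysis does not use the class, reporting of serious events within 24 hours under Section 11.2 does not depend on it, and the protocol contains no stopping rule that refers to it. It should be corrected, but it is not critical.

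**What to change.** Reword Section 11.1 as follows:

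- Remove the condition that an intervention-related event must be absent from the control arm, and the clause that makes an increase irrelevant.
- Use one event list for both arms. Count every event by arm regardless of presumed cause and compare the arms with the tests already planned in Section 12.1. For events with a surgical background, this comparison is the main evidence of harm.
- Take relatedness from the per-event judgement already recorded under Section 11.2, whether or not any control had the same type of event.
- Reconcile the two lists, in particular for decreased range of motion and knee swelling.
- Grade severity as mild, moderate or severe, and record seriousness as a separate yes/no item using the six existing criteria.

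The cost is the rewording of one section and one extra field on the adverse event form. As a protocol change it goes to the institutional review board under Section 13. No visits, staff or participants are added.

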## **11.2 Record and Report**

Once an AE occurs, the time of occurrence, clinical manifestation, treatment process and duration, relation with intervention, and outcome of the AE should be recorded in detail on the case report form. After an unintended sign (such as laboratory test abnormalities) occurs, the patient must be followed up until the test results return to normal, or return to pre-intervention levels, or the AE is determined to be unrelated to the intervention. In cases of SAEs, an SAE form must be filled in and reported to the institutional review board (IRB) (within 24 hours) and National Medical Products Administration (if applicable).

## **Section 12. Statistical Analysis**

### **12.1 Primary Analysis**

The primary analysis will be performed following the intention-to-treat principle, which emphasizes on the original group allocation by randomization. Specifically, once a participant is enrolled and undergoes randomization, the baseline and outcome measures will be included in the allocated group, regardless of whether the participant violates the protocols and whether the participant is dropout during follow-up: (1) if a participant is randomized to the intervention group but does not receive 3 doses of PRP injection, this participant will not be

excluded from the intervention group; (2) if a participant is randomized to the control group but receives knee injection out of the protocol, this participant will not be excluded from the control group; (3) if a participant is randomized to either group but lost to follow-up, this participant will not be excluded from the primary analysis, either. In principle, the primary analysis should include all participants randomized in this study. For the missing data, simple or multiple imputation will not be performed in the primary analysis.

All statistical analyses will be performed using the IBM SPSS software, with a 2-sided significance level of 0.05. Descriptive statistics will be presented as mean and SD (for normally distributed values), median and interquartile range (for non-normally distributed values), or number and percentage (for categorical variables).

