## **4.3 Criteria of Protocol Violation**

Participants included in the study should be classified as protocol violation (not excluded in the intention-to-treat analysis but excluded in the per-protocol analysis) if they meet any of the following criteria:

- ① Participants in the intervention group who fail to receive the intervention protocols (receiving 0, 1, 2, or >3 doses, or 3 doses with violation of injection schedules);
- ② Participants in both groups who undergo reoperation (including debridement, lysis of adhesion, revision ACLR, and other knee surgeries) or receive knee injection out of the protocol (including PRP, sodium hyaluronate, and other medications).

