### **Section 5. Sample Size**

The minimal clinically important difference (MCID) of the primary outcome varies among studies, ranging from 8 to 40 for each subscale among patients with knee injuries or osteoarthritis. Based on the anchor-based method, the MCIDs are 10.7–16.7 for the 4 subscales, averaged 13.8. Therefore, the statistical hypothesis is based on detecting a between-group difference of 13 points. The maximum SD is estimated to be 20 points, thus the effect size is 0.65. With the 2-sided significance level and power setting at 0.05 and 0.9, respectively, a sample size of 51 participants is required in each group (1:1 allocation, calculated using G\*Power 3.1, based on the test of mean difference between two independent groups, and assuming a balanced baseline). After adding the dropout (estimated within 15%), a total of 120 participants (60 in each group) should be included in this study.

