#### ③ Other variables

The Kolmogorov-Smirnov test will be applied to evaluate the normality for continuous variables. The Student t test will be used for comparison of continuous variables with normal distribution. The Mann-Whitney-Wilcoxon test will be used for comparison of non-normally distributed continuous variables and ordinal variables (including GROC, amount of ACL

remnant, and grades of knee laxity). The Pearson chi-square test or Fisher exact test will be used for comparison of categorical variables (including demographic data and adverse events), depending on expected frequencies for the contingency tables.

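### Neither planned adverse-event comparison counts harms among everyone who received at least one PRP injection

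*Protocol*

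**What the plan says.** Section 12.1 follows the intention-to-treat principle: "the baseline and outcome measures will be included in the allocated group, regardless of whether the participant violates the protocols". It spells out that PRP participants with fewer than three doses stay in the PRP arm, and that a participant "randomized to the control group but receives knee injection out of the protocol" stays in the control arm. The schedule in Section 9 lists adverse events under outcome measures. Item ③ of 12.1 gives the chi-square or Fisher exact test for "comparison of categorical variables (including demographic data and adverse events".

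Section 12.2 plans per-protocol (as-treated) analyses for all outcomes, by the same methods. Section 4.3 sets the violation criteria. In the intervention group these are "receiving 0, 1, 2, or >3 doses" and three doses given off schedule. In both groups they are reoperation and knee injection outside the protocol, whether PRP, sodium hyaluronate or another drug. Section 12.2 excludes such participants, except that someone who followed exactly the other group's protocol is moved to that group.

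Section 11.1 defines intervention-related adverse events as those that occur only in the intervention group and are probably related to the intervention. Section 11.2 has each event's relation to the intervention recorded on the case report form.

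**The concern.** A statement about the harms of an injection needs a denominator of people who were injected, and a numerator that keeps all their reactions. Analysis by allocation guards the efficacy comparison, but for injection harms it mixes in people who could not have had the reaction. A per-protocol set has the opposite fault: stopping early or having further surgery may itself be the result of a harm. If the plan has only these two sets, one dilutes the reaction risk and the other may remove reactions selectively. The safety statement for a repeated intra-articular injection would then rest on two tables that can both read low.

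**Working it through.** **Step 1. Where each kind of participant is counted**

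| Participant | Given PRP? | 12.1, by allocation | 12.2, per protocol (as treated) |
|---|---|---|---|
| PRP arm, 0 doses | No | PRP | Leaves the PRP group (excluded, or moved to control) |
| PRP arm, 1, 2, >3 or off-schedule doses | Yes | PRP | Excluded |
| PRP arm, dosed to plan, then reoperated | Yes | PRP | Excluded |
| Control, exact PRP protocol | Yes | Control | Moved to PRP |
| Control, some PRP | Yes | Control | Excluded |
| Control, other injection | No | Control | Excluded |

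Neither analysis column matches the second column. The 12.1 column fails for zero-dose PRP participants and for controls given PRP. The 12.2 column fails for partly dosed, overdosed, off-schedule and reoperated participants.

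**Step 2. The plan's own figure**

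The arm size comes from Section 5: "detecting a between-group difference of 13 points" with an SD of 20 gives 13/20 = 0.65. At two-sided 0.05 and power 0.9, the two-sample t test needs 50.7, so 51 per group. Then 51/0.85 = 60 per arm. The stated figures reproduce, and nothing in this point changes them.

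**Step 3. Dilution by allocation**

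Let r be the reaction risk per injected participant and U the number never injected, with u = U/60. Neither is in the documents. Assumed ranges: r from 10% to 30%, U from 0 to 9.

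PRP-arm risk by allocation = r × (60 − U)/60 = r × (1 − u)

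| U | 1 − u | r = 10% | r = 20% | r = 30% |
|---|---|---|---|---|
| 0 | 1.00 | 10.0% | 20.0% | 30.0% |
| 3 | 0.95 | 9.5% | 19.0% | 28.5% |
| 6 | 0.90 | 9.0% | 18.0% | 27.0% |
| 9 | 0.85 | 8.5% | 17.0% | 25.5% |

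**Step 4. Loss of events in the 12.2 set**

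If k exposed participants are excluded for partial dosing and carry the average risk, the expected reactions lost are k × r: from 3 × 0.10 = 0.3 to 9 × 0.30 = 2.7. If they stopped because of a reaction, the loss is k itself. For example, 60 injected at r = 20% gives 12 reactions. If 3 of those 12 participants stopped for that reason, the 12.2 set shows 9/57 = 15.8% instead of 12/60 = 20%.

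**Step 5. Classification**

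Under 11.1 an event must occur in the intervention group to be intervention-related. A reaction in a control given PRP therefore fails the definition, whatever relation the case report form records under 11.2.

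**The case against.** The strongest reply is that a reader might infer the plan compares harms by allocated arm only. It does not. Section 12.2 covers all outcomes, takes zero-dose participants out of the PRP group, and moves or excludes injected controls. That stands, and it rules out any claim that dilution goes unaddressed.

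A reader might also infer that reactions in injected controls systematically count against the control arm. The documents do not support this in general. Off-protocol injections need not be PRP, so the PRP reaction risk cannot be assigned to all of them, and 12.2 removes or moves these controls. Section 11.2 also identifies reactions by individual attribution, which helps. It does not replace a comparison by exposure, because decreased range of motion, for one, is listed in 11.1 both as a possible intervention-related event and as a common one.

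A third stronger reading is that uninjected participants are likely and a known amount of risk is hidden. A zero-dose participant must miss injection at three routine visits, no rates are given, and no confidence bound for adverse events is planned that could be called wrong.

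It can also be said that Section 10 does not list adverse events as outcomes, and that safety sets are often left to a statistical analysis plan. If adverse events are not outcomes, both rules lose their hold on them and still no exposed set exists. A separate plan could add the set, but the 12.2 exclusions and the 11.1 definition are stated here and would still have to be overridden.

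Finally, leading with treatment received for every adverse event would be unsound. Graft failure or arthrofibrosis can arise in the 4 weeks before the first injection, and an early complication may be why someone is not injected. This stands and shapes the fix.

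**Conclusion.** The point holds in this limited form: the plan has two adverse-event comparisons, neither in the exposed population, and the definition in 11.1 adds to the gap. The direction for injection reactions is towards understatement, by the factor (1 − u) in the allocated-arm table. In the 12.2 set it depends on how many exposed participants are dropped because of a harm. The actual size is unknown. Over the assumed range of 3 to 9 uninjected of 60, the allocated-arm risk is 5% to 15% too low in relative terms, and with none uninjected that bias vanishes. The efficacy analysis, the primary outcome and the sample size are unaffected.

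**What to change.** Add to Section 12 a safety set along these lines:

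> The safety set comprises all randomised participants, grouped by receipt of at least one PRP injection versus none. No participant is excluded for partial, additional or off-schedule dosing or for reoperation. Injection-related adverse events are summarised in this set, and also per injection given. Common adverse events, such as graft failure and arthrofibrosis, are compared by allocated arm.

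In Section 11.1, define intervention-related events by exposure to PRP and probable relation to it, rather than by arm.

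The cost is one extra table. Doses received are already needed for the criteria in 4.3, and relation to the intervention is already recorded under 11.2. The drawback is that the comparison by exposure is not strictly randomised, which is why the allocated-arm table stays alongside it.
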